#### 6.2.4 DOSE MODIFICATION AND DELAYS

Dose modification of 1800 mg Dara-SC (increase or decrease) is not permitted. In total, 8 Dara-SC injections are planned, particularly 2 cycles of 4 injections administered weekly. Changes of dosing interval should not affect the following study drug administration, unless the previous dose was administered within the previous 3 days, because a minimum of 4 days between daratumumab doses is required. If doses of the study drug are skipped, they will not be additionally included in the treatment schedule. An extension of treatment period is not allowed. Subjects will continue to receive study treatment until Week 8, unless occurrence of unacceptable toxicity, or other reasons as listed in Section 8.2 DISCONTINUATION OF STUDY TREATMENT.

Dose delay resembles a method for managing potential occurring daratumumab-related toxicities. Before each dose of study drug, the subject will be evaluated by the treating physician for possible toxicities that may have occurred after the previous dose(s). Delay in study drug administration will be based on the toxicity experienced during the previous injections. Toxicities are to be assessed according to NCI-CTCAE, Version 5.0 (see also section 10.3 SEVERITY CRITERIA).

The study treatment must be held if any of the following criteria are met, to allow for recovery from toxicity, regardless of relationship to study drug:

- Grade 3 or higher hematologic toxicity
- Grade 3 or higher non-hematologic toxicities
- Febrile neutropenia
- Hypogammaglobulinemia requiring IVIG substitution according to criteria provided in section 6.4.3 IMMUNOGLOBULINE SUBSTITUTION

Study treatment should be resumed when the toxicity has resolved to  $\leq$  Grade 2 except for laryngeal edema, bronchospasm or febrile neutropenia, which must be fully recovered (see also section 7.6.2 INJECTION RELATED REACTIONS AND INJECTION SITE REACTIONS). Infusion-related reactions may occur upon re-initiation of daratumumab after a prolonged delay in treatment. Investigators should consider the applicable infusion reaction guidance provided in sections 6.2.2 (PREDOSE MEDICATION) and 6.2.3 (POSTDOSE MEDICATION). Subjects missing  $\geq 3$  consecutive planned doses of study drug for reasons other than toxicity should be withdrawn from treatment, unless, upon consultation with the sponsor and the review of safety and efficacy, continuation is agreed upon.

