### 8.2 DISCONTINUATION OF STUDY TREATMENT

A participant will not be withdrawn from the study if he or she has to discontinue study agent before the end of the treatment regimen.

A subject's study agent must be discontinued if:

- Inclusion or exclusion criteria violation was noted after the subject started study drug, when continuation of the study drug would place the subject at risk as determined by the Investigator
- the Investigator, sponsor, and/or medical monitor believes that for safety reasons or tolerability reasons (e.g. adverse event), or due to severe, unstable, or rapidly progressive SLE disease activity, it is in the best interest of the subject to discontinue study agent.
- The subject (or the subject's legally acceptable representative) withdraws consent for administration of study drug.
- the subject develops study agent hypersensitivity (e.g. anaphylaxis, angioedema) reaction that is reported as serious or severe.
- the participant develops a serious opportunistic infection or SARS-CoV-2 infection confirmed by positive PCR-test (the follow-up phase can be continued once quarantine/COVID-symptoms/SARS-CoV-2 PCR positivity have resolved).
- if a new immunomodulator that is permitted per-protocol is initiated, then a participant will be considered a treatment failure but will not need to be withdrawn from the study.
- Occurrence of serious adverse events which are not compatible with the further administration of the study drug.

It is recommended that follow-up visit should be continued although patients might have discontinued study drug or had temporarily halt of study drug.

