### 8.3 WITHDRAWAL FROM STUDY

A participant will be withdrawn from the study for any of the following reasons:

1. Withdrawal of consent to participate.
2. Lost to follow-up.
3. Death.
4. Subject is significantly non-compliant with study procedures, including inconsistent study drug dosing, which would put the subject at risk for continued participation in the trial as determined by the Investigator.
5. Enrollment in any other clinical study involving an investigational product or enrollment in any other type of medical research judged not to be scientifically or medically compatible with this study.
6. Decision by the investigator or sponsor in case of any adverse event that justifies withdrawal and is in the best interest of the subject. The following reasons automatically lead to the discontinuation of the study participation:
  - a. The Investigator believes it is in the best interest of the subject.
  - b. Subject develops an ECG change considered clinically significant.
  - c. The subject becomes pregnant.
  - d. The subject is diagnosed with a malignancy, with the exception of no more than 2 localized basal cell skin cancers that are treated with no evidence of recurrence or residual disease.
  - e. the subject is deemed ineligible according to the following TB criteria: A diagnosis of active TB is made or a subject undergoing evaluation has a chest

- radiograph with evidence of current active TB and/or a positive QuantiFERON®-TB test result, unless active TB can be ruled out.
- f. Subject develops a GI perforation.
  - g. If a diagnosis of deep vein thrombosis, pulmonary embolus, or non-cardiac, non-neurologic arterial thrombosis is confirmed.
  - h. Subject develops active neuropsychiatric SLE (excluding lupus headache) as defined by the CNS portion of SLEDAI-2K or BILAG.
  - i. HBcAb positivity with HBV DNA above the lower limit of quantification
  - j. Positive HIV test

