## 9.2 SAMPLE SIZE DETERMINATION

The primary objective of this exploratory study is to evaluate whether treatment with the anti-CD38 antibody daratumumab is associated with a significant reduction of pathogenic serum anti-dsDNA antibodies in patients with moderate to severe SLE. Results from two patients treated with daratumumab in our institution (compassionate use) resulted in a mean reduction of anti-dsDNA antibodies by 250 IE/ml (SD 121) what corresponds to a reduction of about 50% at 90 days follow-up after first dose of daratumumab. It yields an effect size of 2.1. A sample size of 5 patients is necessary to show a significant reduction in anti-dsDNA antibodies by a two-tailed Wilcoxon signed-ranked test for matched pairs between baseline and the 12-week follow-up visit, assuming a statistical power of 80% and a type one error rate of 5%. We conservatively assume a drop-out rate of 50%. Therefore, a total of 10 patients will be enrolled in this exploratory study. Sample size calculation was performed with G\*Power version 3.1.9.2.

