### 9.3 ANALYSIS SETS

All patients who were enrolled into the study are included in the main analyses. In fact, the primary and secondary outcome measures are analyzed according to the intention-to-treat principle. In addition, a modified intention-to-treat analysis is planned, excluding patients with a dose interruption in case of an adverse event or discontinuation of study treatment for other reasons, such as use of prohibited medication (see section 6.6). A complete case analysis is performed as sensitivity analysis.

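### Follow-up after stopping study drug is only recommended (8.2), so observed Week 12 titres needed by the intention-to-treat primary analysis can be lost avoidably

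*Protocol*

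**What the plan says.** Section 8.2 opens by stating that a patient who has to stop study agent early stays in the study. It closes on a softer note: "It is recommended that follow-up visit should be continued although patients might have discontinued study drug or had temporarily halt of study drug". After SARS-CoV-2 infection, 7.1 and 8.2 likewise permit follow-up without requiring it.

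Section 9.3 states that "the primary and secondary outcome measures are analyzed according to the intention-to-treat principle", with all enrolled patients in the main analyses. The primary endpoint (3.2.1) is the anti-dsDNA titre at Week 12 against baseline. Section 9.4 fills missing primary values with the last known value. Section 9.3 adds a modified intention-to-treat set, which excludes adverse-event interruptions and treatment discontinuations, and a complete-case sensitivity analysis.

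Three sections deal with patients whose dosing goes wrong:

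- 6.2.4: those missing three or more "consecutive planned doses of study drug for reasons other than toxicity should be withdrawn from treatment", unless continuation is agreed with the sponsor.
- 8.2: study agent is stopped when this is judged to be in the subject's best interest for safety, tolerability or disease-activity reasons.
- 8.3: item 4 lists among the reasons for leaving the study "Subject is significantly non-compliant with study procedures, including inconsistent study drug dosing, which would put the subject at risk", as the investigator determines. Item 6a lists the investigator's view of the subject's best interest among the reasons that automatically end participation.

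For withdrawals decided by sponsor, physician or participant, 8.3 then provides an early termination visit with the Week 36 (or Week 84) procedures and a visit 8 weeks after the last dose to record adverse outcomes.

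**The concern.** An intention-to-treat analysis at a fixed time needs the outcome at that time from every enrolled patient, whether or not dosing was completed. Section 8.2 makes the visits that supply it optional for exactly those patients whose dosing was cut short. This includes patients on a temporary halt, who are expected to resume.

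The other planned analyses do not repair the gap. The modified set excludes patients who discontinued, and the complete-case analysis drops anyone without an observed value. A patient who stopped dosing and has no Week 12 sample is therefore represented only in the main analysis, and only by an earlier titre. With 10 patients, each such substitution carries weight.

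The overlap among 6.2.4, 8.2 and 8.3 adds to this. Where more than one rule applies to a patient, the text does not settle whether that patient stops treatment and is followed to Week 12, or leaves the study.

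**Working it through.** **The plan's own figure.** Section 9.2 takes a mean fall of 250 IE/ml with SD 121, from two patients. The ratio 250/121 = 2.07 is stated as 2.1. The test is planned as significance "by a two-tailed Wilcoxon signed-ranked test for matched pairs between baseline and the 12-week follow-up visit", at 80% power and 5% two-sided error. With the asymptotic relative efficiency method, power comes from a noncentral t with n' = n × ARE, n' − 1 degrees of freedom and noncentrality 2.1 × √n':

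| n | ARE 3/π | ARE 0.864 |
|---|---|---|
| 4 | 75.0% | 65.1% |
| 5 | 91.0% | 85.0% |

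Five is the smallest n with at least 80% power, and 5/(1 − 0.50) = 10. Both figures reproduce, and this point changes neither.

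**What each observed Week 12 value is worth.** Section 9.5.1 reports the median change with a 95% confidence interval. The protocol names no method, so I assume the order-statistic interval.

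- 10 observed values, 2nd to 9th: 1 − 2 × (1 + 10)/1024 = 97.9%.
- 5 observed values, minimum to maximum: 1 − 2/32 = 93.75%, the widest available and below 95%.

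The second line describes a complete-case analysis after the planned 50% drop-out. Under carry-forward the main analysis still has 10 entries, but up to 5 would not be Week 12 observations.

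**Do the visits after withdrawal supply the value?** The Week 12 visit is Day 77 ± 3, that is Days 74 to 80. The visit 8 weeks after the last dose falls as follows:

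- last dose Day 14: 14 + 56 = Day 70, outside the window;
- last dose Day 21: 21 + 56 = Day 77, the Week 12 day itself.

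In the second case the patient is seen on the right day, but 8.3 describes the visit only as recording adverse outcomes and names no titre. The early termination visit does include anti-dsDNA, because the schedule marks it at Week 36. It is timed by the withdrawal, however, and not by Week 12.

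**Direction under carry-forward.** Suppose k of 10 patients have no Week 12 sample, the other 10 − k fall by 250, and the carried value shows half of that fall (125). The analysed mean fall is 250 × (1 − k/10 × 0.5). The true mean depends on what happened to the k patients after they stopped:

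| k | Analysed mean | True mean, full fall in all | Error | True mean, no fall in the k | Error |
|---|---|---|---|---|---|
| 2 | 225 | 250 | −25 | 200 | +25 |
| 5 | 187.5 | 250 | −62.5 | 125 | +62.5 |

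The carried fraction and both true courses are assumptions. If all patients truly fall by 250 and the carried fraction is 0% or 75%, the analysed mean is 200 or 237.5 for k = 2, and 125 or 218.75 for k = 5. I use means for simple arithmetic; the plan reports medians.

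**The case against.** The case for leaving the text alone has substance. Section 8.2 does open by keeping these patients in the study, and the visit schedule makes no exception for patients off drug, so a site may well perform the visits anyway. The trial is single-centre and exploratory, with no confirmatory test. All of this is true and limits the weight of the point. It does not turn a recommendation into a requirement.

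Several stronger readings are tempting, and the protocol does not support them:

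- *That 8.3 removes every inconsistent doser and so flatly contradicts 6.2.4.* Item 4 needs significant non-compliance that puts the subject at risk, in the investigator's judgement. The 6.2.4 trigger is different and has an exception. A patient can meet one without the other, so this is an overlap to reconcile.
- *That these patients drop out of the intention-to-treat analysis.* They stay in it through carry-forward. What is lost is the observed Week 12 value.
- *That the carried value always comes from the dosing period.* After withdrawal it may come from the early termination visit, which includes serology.
- *That the primary result shifts towards patients who completed dosing.* That could describe the complete-case analysis. Under carry-forward the error can go either way, as the table shows.
- *That the planned 50% drop-out measures the loss.* It is an all-cause assumption that the protocol calls conservative. Nothing assigns a share to optional visits, and part of it (withdrawn consent, loss to follow-up, death) could not be sampled in any case.

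**Conclusion.** The point holds in a limited form. Section 8.2 leaves the Week 12 sample optional for patients off drug, while 9.3 needs it from everyone enrolled and 9.4 replaces what is missing with an earlier value. Some of that missingness is avoidable, because the visit is already scheduled and 8.2 says these patients remain in the study.

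The size cannot be fixed from the protocol, which gives neither the number affected nor the course of the titre after early stopping. Under the assumptions shown, the error in the mean fall reaches 25 IE/ml with 2 patients affected and 62.5 with 5, in either direction, against an expected 250. The upper case takes the whole planned drop-out as avoidable, which it is not.

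The overlap among 6.2.4, 8.2 and 8.3 items 4 and 6a is real but secondary. The clearest instance is the subject's best interest, which leads to stopping drug in 8.2 and to leaving the study in 8.3.

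**What to change.** In 8.2, replace the closing recommendation by a requirement: after study drug is stopped or interrupted, the scheduled visits, at minimum the Week 12 anti-dsDNA sample, are performed whatever the treatment status, unless consent to follow-up is withdrawn.

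Separately, the sponsor should reconcile 6.2.4, 8.2 and 8.3 items 4 and 6a so that it is clear when a patient stops treatment only and when a patient leaves the study. Which withdrawal rule should apply is a clinical matter for the sponsor and is not proposed here.

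The cost is a short amendment. No procedure is added, because the visit and the sample are already in the schedule. The downside is the effort of bringing back patients who have stopped dosing.

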### 8.3 WITHDRAWAL FROM STUDY

A participant will be withdrawn from the study for any of the following reasons:

1. Withdrawal of consent to participate.
2. Lost to follow-up.
3. Death.
4. Subject is significantly non-compliant with study procedures, including inconsistent study drug dosing, which would put the subject at risk for continued participation in the trial as determined by the Investigator.
5. Enrollment in any other clinical study involving an investigational product or enrollment in any other type of medical research judged not to be scientifically or medically compatible with this study.
6. Decision by the investigator or sponsor in case of any adverse event that justifies withdrawal and is in the best interest of the subject. The following reasons automatically lead to the discontinuation of the study participation:
  - a. The Investigator believes it is in the best interest of the subject.
  - b. Subject develops an ECG change considered clinically significant.
  - c. The subject becomes pregnant.
  - d. The subject is diagnosed with a malignancy, with the exception of no more than 2 localized basal cell skin cancers that are treated with no evidence of recurrence or residual disease.
  - e. the subject is deemed ineligible according to the following TB criteria: A diagnosis of active TB is made or a subject undergoing evaluation has a chest

- radiograph with evidence of current active TB and/or a positive QuantiFERON®-TB test result, unless active TB can be ruled out.
- f. Subject develops a GI perforation.
  - g. If a diagnosis of deep vein thrombosis, pulmonary embolus, or non-cardiac, non-neurologic arterial thrombosis is confirmed.
  - h. Subject develops active neuropsychiatric SLE (excluding lupus headache) as defined by the CNS portion of SLEDAI-2K or BILAG.
  - i. HBcAb positivity with HBV DNA above the lower limit of quantification
  - j. Positive HIV test

In the event of withdrawal from the study through a decision by the sponsor, the investigating doctor or the study participant, the early termination visit will be carried out (which is equivalent to the visitation procedures at Week 36 of the core study period or Week 84 in the LTE observational period). Furthermore, a follow-up visit will be held, recording the adverse outcomes with an interval of 8 weeks after the last administration of the study drug (final study visit). The participants in the study will be transferred for further rheumatological treatment to the respective responsible/referring treatment institution after the study has been concluded.

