### 3.1.4 PRIMARY OBJECTIVE OF THE LTE OBSERVATIONAL PERIOD

1. To evaluate of the long-term safety of daratumumab, previously administered in the core study period, for the treatment of SLE

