#### 7.6.4 ELECTROCARDIOGRAM

A 12-lead ECG will be performed during the screening visit and in week 36. During an ECG, it is advised that the test subjects are in a quiet environment without distraction (e.g. television, cell phones) and lie in a supine position. The patient should rest for at least 5 minutes before the ECG recording and should not speak or move their arms or legs. If an abnormal result is recorded, the ECG should be repeated.

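### Section 8.3 item 6b ends study participation, not only study drug, for any ECG change judged clinically significant at any time, and so can drop patients with a possible cardiac signal from safety follow-up

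*Protocol*

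**What the plan says.** Protocol section 8.3, item 6, introduces a list of ten events (a to j) with "The following reasons automatically lead to the discontinuation of the study participation". Item 6b reads "Subject develops an ECG change considered clinically significant". It has no time limit and no link to dosing. Item 6a separately allows withdrawal when "The Investigator believes it is in the best interest of the subject", and item 1 covers withdrawal of consent.

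Section 8.2 treats stopping the drug differently. A patient who has to stop study agent is not thereby withdrawn, and the section ends: "It is recommended that follow-up visit should be continued although patients might have discontinued study drug or had temporarily halt of study drug".

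On timing, section 7.6.4 says "A 12-lead ECG will be performed during the screening visit and in week 36", and an abnormal ECG is to be repeated. The LTE schedule marks ECGs at Week 36 (LTE entry) and Week 84 (last visit).

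Section 8.3 reaches into the extension: its early termination visit follows the procedures of "Week 36 of the core study period or Week 84 in the LTE observational period". After a withdrawal, "a follow-up visit will be held, recording the adverse outcomes with an interval of 8 weeks after the last administration of the study drug", and the protocol labels this the final study visit. Section 3.1.4 gives the primary objective of the LTE: "To evaluate of the long-term safety of daratumumab, previously administered in the core study period, for the treatment of SLE".

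**The concern.** A withdrawal rule triggered by a safety finding should protect the patient from further drug. Item 6b goes further and ends observation as well, whether or not any drug remains to be given. Section 8.2 keeps patients in the study after serious hypersensitivity or a serious opportunistic infection, and no reason is given for handling an ECG change differently.

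At stake is the completeness of safety follow-up in exactly the patients in whom it matters most. Section 3.2.3 names cardiovascular events as an area of safety interest, and the LTE primary endpoint counts serious adverse events through the end of study. Section 9.4 does not replace missing safety data. The loss is therefore informative: patients leave because of a safety signal, and what happens to them afterwards is not collected at any planned visit.

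**Working it through.** **Inputs.** Last planned dose at Week 8, Day 49, with no extension of treatment (section 6.2.4 and schedule). Core follow-up of 28 weeks and LTE follow-up of 48 weeks (section 1.5). LTE visits at Weeks 42, 48, 54, 60, 66, 72, 78 and 84. Target enrolment of 10 patients.

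**The plan's own figure.** Week 36 − Week 8 = 28 weeks, and 4 + 8 + 28 = 40 weeks, as section 1.5 states. In days, with Day = 7 × (week − 1), Week 36 is Day 245, and (245 − 49)/7 = 28.0 weeks. The schedule prints Day 241, which gives (241 − 49)/7 = 27.4 weeks. The difference does not matter here.

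**Where the rule can act at a planned post-dose ECG.**
- Week 36: dosing ended 28 weeks earlier, so there is no drug to withhold.
- Week 84: this is the final visit, so withdrawal ends nothing.

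Among the ECGs planned in 7.6.4 and the LTE schedule, Week 36 is thus the only post-dose one at which 6b has a consequence, and that consequence is the end of observation.

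**What is lost at Week 36, if 6b bars LTE entry.** Eight visits over 84 − 36 = 48 weeks. Of the 84 − 8 = 76 weeks after the last dose, that is 48/76 = 63% for that patient. If all 10 patients entered the LTE, the plan would hold 10 × 8 = 80 visits and 10 × 48 = 480 patient-weeks, so one patient is 8/80 = 48/480 = 10%.

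**Whether a later contact replaces it.** The visit 8 weeks after the last dose falls on Day 49 + 56 = Day 105, which is Week 16. That is 36 − 16 = 20 weeks before Week 36 and already past. The early termination visit repeats Week 36 procedures.

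**Which events are lost.** Section 9.8.1 defines treatment-emergent events by onset in the treatment phase or worsening of a pre-existing condition. Most new events during the LTE would not qualify, so the loss is mainly of serious adverse events. The ECG event itself is still recorded and analysed.

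**Unscheduled ECGs.** An ECG taken for symptoms can trigger 6b at any time. Before Week 12 (Day 77), automatic withdrawal also removes the visit at which the primary endpoint is measured, and section 9.4 would then carry the last anti-dsDNA value forward.

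**Precision.** With no events, the exact two-sided 95% upper limit is 1 − 0.025^(1/n): 30.8% for n = 10 and 33.6% for n = 9. Even if the withdrawn patient left the denominator altogether, the change is small.

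**Other triggers.** Four of the ten events in item 6 (d malignancy, e active TB, f GI perforation, g thrombosis) are also areas of safety interest in section 3.2.3. The protocol names these outcomes and then stops observing the patients who have them.

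**The case against.** *Week 36 need not cost the LTE.* Under 8.1 a patient assessed through Week 36 has completed the core study, and the LTE entry criteria in 5.3 contain no ECG condition. This stands as a limit: losing the whole LTE at Week 36 depends on 8.3 overriding 5.3. The text leaves this open, since 8.3 ends study participation and explicitly provides for the LTE.

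*The rule matters mainly during dosing.* A reader might infer that 6b can act only at Week 36. The documents do not support that. Unscheduled ECGs can trigger it at any time, and sections 3.2.2 and 3.2.3 list ECGs among evaluations with a time frame of each visit. The Week 36 statement holds only for the ECGs planned in 7.6.4 and the LTE schedule. During dosing, stopping the drug is sensible, but that does not require ending follow-up.

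*The trigger is a clinical judgement.* It is, and an abnormal ECG is repeated first. Once the judgement is made, however, the consequence is automatic, and 6a already gives the investigator discretion without 6b.

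*Section 10.5 records adverse events until the last patient's last follow-up visit.* That is the general recording period. It schedules no contact with a withdrawn patient, for whom 8.3 calls the visit 8 weeks after the last dose the final one. Where the protocol wants follow-up after exclusion it says so, as for pregnancy in 7.6.7.

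*The size is unproven.* This stands. No rate of such ECG changes is given.

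**Conclusion.** The concern holds as an inconsistency between 8.3 item 6b on one side and 8.2 and the LTE safety objective on the other. Followed as written, the rule ends observation of patients because of a safety finding, even when no drug remains to be stopped.

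For one patient affected at the planned Week 36 ECG, the cost is up to 8 visits and 48 weeks. This assumes that the patient would have consented to the LTE and that 8.3 prevails over 5.3. For a patient affected before Week 12 through an unscheduled ECG, it also includes the primary-endpoint visit. At the planned post-dose ECGs the Week 12 analysis is untouched.

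A reader might go further and picture the LTE event proportion falling from 1/10 to 0/9. The documents do not support that as an expected result. It supposes that the withdrawn patient would have had the only later serious event, and it drops that patient from the denominator, whereas section 9.3 keeps all enrolled patients in the main analyses. The point is selective loss of safety follow-up, at unknown frequency and with little effect on precision.

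**What to change.** 1. Move 6b from 8.3 to the list in 8.2, as a reason to stop study drug with follow-up continued.
2. State in both 8.3 and 5.3 that an ECG change after the last dose neither ends participation nor bars entry into the LTE.
3. Keep withdrawal by consent (item 1) and by investigator decision (6a).
4. Apply the same approach to the other triggers that 3.2.3 names as areas of safety interest, at least d (malignancy), f (GI perforation) and g (thrombosis): stop drug, and keep safety follow-up where the patient agrees.

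As an editorial matter, add Week 84 to 7.6.4 and remove ECGs from the each-visit time frame in 3.2.2 and 3.2.3, so that the ECG schedule reads the same throughout.

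The cost is an amendment to wording. No procedures are added, because the patient attends visits already planned, and neither patient nor investigator loses the option of withdrawal.
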